## Abstract

**Background:**

Ageing is associated with a range of anatomical and physiological changes. Establishing whether a change is part of ‘normal’ ageing or the early signs of disease will affect management strategies. Progressive stiffening of the thoracic spine, decreasing chest wall compliance and declining lung function begin as early as 40 years of age. Administering an intervention such as manual therapy, which has the potential to mitigate age-related changes in the thoracic spine and chest wall, has the potential to improve thoracic compliance and lung function. The aims of this trial are to investigate whether manual therapy can mitigate the effects of age-related changes in lung function and whether there is a difference in effect between different forms of manual therapy.

**Methods:**

The study design is a randomised controlled trial of 372 people with no history of respiratory disease between the ages of 50 and 65 years. The cohort will be divided into three equal groups. The first group will receive a simple 10-min treadmill walking program (Ex). The second group will receive joint mobilisation (MB) of the thoracic spine and ribs plus the same walking program (MB + Ex). The third group will receive joint manipulation (MT) of the thoracic spine and ribs plus the same walking program (MT + Ex). All interventions will be administered a total of six times over a 3-week period. The primary outcome measure is lung function: forced expiratory volume in the 1st second and forced vital capacity. The secondary outcome measures include chest wall expansion (tape measurements) and quality of life measurements (36-Item Short Form Health Survey). Outcome measurements will be taken by blinded assessors on four occasions over a 9-week period. Adverse event data will be gathered at the beginning of each intervention session.

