### Outcome measurements

The primary outcome measure is lung function: FEV_1_ and FVC. The secondary outcome measures include chest wall expansion (tape measurements) and quality of life measurements (36-Item Short Form Health Survey, SF-36). The metric for these measures is mean change from baseline. All outcome measurements will be taken by blinded assessors on four occasions over a 9-week period: at baseline and then at weeks 3, 6 and 9.

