**Fig. 2 Fig2:**
[figure not shown]
SPIRIT figure showing times points for enrolment, interventions and assessments. *Ex* exercise, *MB* mobilisation, *MT* manipulation, *FEV*_*1*_ forced expiratory volume in the 1st second, *FVC* forced vital capacity, *SF-36* 36-Item Short Form Health Survey

All MB and MT will be administered by students enrolled in the Masters of Osteopathic Medicine program at Southern Cross University who have been trained in the relevant manual therapy techniques used in this trial. They will be under supervision at all times by a registered osteopath.

A manipulation will be deemed successful by the presence of an audible release. All releases will be recorded on the participant’s file by the treating intern as either ‘absent’ (0), ‘single’ (1), or ‘multiple’ (2) for each manipulation. Should a deviation from the intervention protocol occur, the supervisor will be on hand to either approve the deviation or ensure a return to protocol. Any protocol violations, whether for clinical or non-clinical reasons, will be recorded on the participant’s file by the treating intern at each intervention session.

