### Data monitoring

The data safety monitoring board (DSMB) appointee who will oversee the study is the Osteopathy Professional Experience Learning Co-ordinator in the School of Health and Human Sciences at Southern Cross University. The DSMB appointee will meet with one or more of the principal investigators on a regular basis to review the study data. As this trial includes the administration of manual therapy by supervised interns, the meetings with the DSMB appointee will focus on safety by reviewing adverse event (AE) data as it is collected during the trial. While severe or unexpected AEs are reported to the relevant Ethics Committee (Institutional Review Board) as a matter of standard procedure in any clinical trial, the DSMB meetings in this trial will track the rate of expected AEs, i.e. the mild to moderate AEs, as a way of monitoring whether participants are being placed at ‘additional’ risk by being treated by interns.

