### Adverse events

The risks of harm or discomfort to participants in this project primarily relate to the potential for AEs resulting from MT intervention. The majority of reported AEs associated with these interventions are mild (muscle soreness and local discomfort), self-limiting, require no further medical attention and resolve within 48 h [19]. Moderate AEs, such as fracture, have also been reported following spinal manipulation and have been estimated to occur at a rate of 1 in 40,000 [20]. Reports of major or catastrophic AEs resulting from spinal manipulation have appeared in the literature with nearly all associated with neck (cervical) manipulation. This trial involves manipulation of the thoracic spine and ribs only and does not include any neck manipulation. The MT techniques used in this trial are similar to the ones used in three previous studies on people with chronic obstructive pulmonary disease (COPD) [16, 17, 21]. There were no major or moderate AEs reported in those studies. Mild AEs associated with MT intervention were reported at a rate of 15% (18 out of 112) in the study on patients with moderate COPD (average age 56.1 years) [16], at a rate of less than 1% (2 out of 403) in the study on patients with moderate to severe COPD (average age 65.5 years) [17] and at a rate of 29% (21 out of 72) in the case series on patients with moderate to severe COPD (average age 79.1 years) [21]. As the trial reported here is being conducted on healthy participants with no history of respiratory disease, it is reasonable to predict that the risk of harm or discomfort to participants will be less than that in the previous studies on people of a similar age with respiratory disease. However, as this trial includes the administration of manual therapy by clinicians with limited clinical experience (interns), we have used an incident rate of 41% for mild AEs, taken from Carnes et al. [19], as the threshold for triggering an automatic halt to the study.

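### The only adverse-event collection time stated, the start of each session, leaves no stated enquiry after session six or for participants who stop attending, so the rate set against the 41% halt threshold may be under-counted

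*Protocol article*

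**What the plan says.** The abstract (Methods) fixes the collection time, "Adverse event data will be gathered at the beginning of each intervention session", and the number of sessions, "All interventions will be administered a total of six times over a 3-week period". The body of the article neither repeats nor extends the collection time.

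Outcome measurements places the assessments "on four occasions over a 9-week period: at baseline and then at weeks 3, 6 and 9" and lists lung function, chest expansion and quality of life. AEs are not mentioned there.

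Data monitoring describes the safety monitor's task as "reviewing adverse event (AE) data as it is collected during the trial", with attention to the rate of mild-to-moderate events. It also says that "severe or unexpected AEs are reported to the relevant Ethics Committee (Institutional Review Board) as a matter of standard procedure".

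The Adverse events section says that most such events are "self-limiting, require no further medical attention and resolve within 48 h". For the automatic halt it states: "we have used an incident rate of 41% for mild AEs".

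**The concern.** An enquiry at the start of a session can learn only about what happened before that session. The sixth session has no successor, so a reaction that develops in the following day or two meets no stated question. A participant who stays away because of soreness after an earlier session has no later session at which to report it. In that second case the missing report depends on the event itself.

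At stake is a decision, not just a descriptive table. The safety monitor follows the rate of expected events because interns give the treatment, and the mild-AE rate triggers an automatic halt. If the count is low, the halt comes late or not at all.

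**Working it through.** The plan states no figure for AE capture, so there is nothing to reproduce. The check counts which post-session intervals have a stated enquiry and then asks what this does to the rate.

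**Inputs.** Six sessions, with an enquiry at the start of each (abstract, Methods); 124 participants per arm (Sample size calculation); threshold 41% (Adverse events).

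**Step 1: coverage.** The enquiry at session 1 precedes any treatment and serves as a baseline. Those at sessions 2 to 6 cover the intervals after sessions 1 to 5.
- Share covered: 5/6 = 83%.
- Sessions per arm at full attendance: 124 × 6 = 744, of which 124 have no stated later enquiry.
- Both manual-therapy arms together: 2 × 744 = 1,488 sessions, of which 248 have none.

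Each treated participant has exactly one last attended session, whether that is the sixth or an earlier one. Participants who leave early are therefore already among the 124 per arm and must not be added to them.

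**Step 2: rate per participant.** Assume the same independent risk p after each session. The true cumulative rate is R = 1 − (1 − p)^6, and the observable rate is 1 − (1 − p)^5 = 1 − (1 − R)^(5/6).

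| True rate R | p per session | Observable rate |
|---|---|---|
| 41% | 8.4% | 35.6% |
| 45% | 9.5% | 39.2% |
| 50% | 10.9% | 43.9% |

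The true rate needed to observe 41% is 1 − 0.59^(6/5) = 46.9%. Under this assumption the halt decision changes only for true rates between 41% and about 47%. At 50% the threshold is crossed despite the gap.

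The answer depends on how events cluster within people. If the same people react after every session, they are found at session 2, and 41% is seen as 41%. If each affected person has exactly one event, equally likely after any session, the observable rate is 41% × 5/6 = 34.2%.

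**Step 3: rate per session followed up.** The sixth session then leaves both numerator and denominator, so with equal risk per session the gap after session six causes no bias. What remains is the loss of participants who leave because of an AE: their last, event-bearing session drops out of the count.

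**Step 4: size of the loss through leaving.** The documents do not say how many participants would leave for this reason. The 10% drop-out allowance in the sample size section is not tied to AEs or to the three treatment weeks, so it does not supply the number.

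**The case against.** The strongest reply is that the evidence is one sentence in the abstract of a condensed article. That sentence says when AE data are gathered; it does not exclude other times. The schedule figure is not shown, and the full protocol may list more collection points. The Outcome measurements section names efficacy measures because that is its subject, so its silence on AEs proves little. This stands, and it limits the point to what is stated. It does not remove the point, because the article does fix a collection time, and followed as written that time leaves the gap.

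Second, there is another route for severe or unexpected events. Sessions are supervised throughout, and "Any protocol violations, whether for clinical or non-clinical reasons, will be recorded on the participant’s file by the treating intern at each intervention session". A reaction during session six would probably be seen. This also stands. It leaves delayed mild-to-moderate events uncovered, and the halt rule rests on the mild ones.

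Third, the article does not say whether 41% is per participant or per session, and on a per-session basis the gap after session six need not matter. That is correct, and the conclusion is made conditional on it.

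Fourth, most such events resolve within 48 h, so questions at weeks 6 and 9 would add little. This is fair, and those two visits are optional in the fix.

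**Conclusion.** The point holds in a limited form. The only stated collection time covers 5 of 6 post-session intervals, with no stated enquiry after session six or for participants who stop attending. Delayed mild-to-moderate AEs may therefore be under-counted. If the halt rate is per participant, it may be too: a true 41% would show as about 36%, assuming equal and independent risk per session. If it is per session followed up, only AE-related leaving would bias it. The percentages are illustrations; the actual under-count cannot be derived from the documents.

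A reader might infer three stronger things that the documents do not support:
- **That AEs are collected only at sessions, and later ones are never recorded.** The article does not say so, and severe or unexpected events have their own route.
- **That drop-outs add a further 12 or so unasked participants per arm (10% of 124).** They are already among the 124 last sessions.
- **That the comparison of harms between arms is biased.** The article describes no such analysis, and whether AE-related leaving would differ between arms is not known.

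**What to change.** Three additions:
1. Ask the same AE questions after session six, at the week 3 visit already scheduled, and optionally at weeks 6 and 9. Use a self-completed form returned to unblinded trial staff, not to the blinded assessor, since talk of treatment reactions could reveal allocation. If the week 3 visit falls on the day of the sixth session, have the form returned a few days later, so that it covers the 48 h in which most of these events occur and resolve.
2. Contact anyone who misses a session or withdraws, and ask the same questions.
3. Include these data in the AE summaries and in the rate that the safety monitor tracks, and state whether that rate is per participant or per session followed up.

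If the full protocol already provides for this, a sentence in the article pointing to it is enough. Otherwise the cost is a short form, a few calls and some care to keep the form away from the assessor. Treatment, randomisation and the primary analysis are unaffected. Recruitment was ongoing when the article was submitted, so the change could still apply to participants treated from then on.

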**Discussion:**

This randomised controlled trial is designed to investigate whether manual therapy can mitigate the effects of age-related changes in lung function and whether there is a difference in effect between different forms of manual therapy. This is the first fully powered trial designed to test this hypothesis on healthy males and females in this age range.

**Trial registration:**

Australian New Zealand Clinical Trials Registry (ANZCTR), 12616001317482. Registered on 20 September 2016.

**Electronic supplementary material:**

The online version of this article (10.1186/s13063-019-3257-z) contains supplementary material, which is available to authorized users.

## Background

Ageing is associated with a range of anatomical and physiological changes involving the cardiovascular, pulmonary and musculoskeletal systems [1–3]. Establishing whether a change is part of ‘normal’ ageing or the early signs of disease is, however, often difficult. In the case of the musculoskeletal system, ‘normal’ age-related changes in the thoracic spine and chest wall include a reduction in spinal muscle thickness, costal cartilage calcification, osteoporosis and spondylosis [4–6]. These changes start to manifest as early as 40 years of age and can lead to progressive stiffening of the spine, decreasing chest wall compliance and declining lung function [5, 7].

As chest wall compliance is a major determinant of static lung volumes, improving compliance leads to improvements in lung volumes. Lung volume is usually assessed using functional lung assessments such as forced vital capacity (FVC) and forced expiratory volume in the 1st second (FEV_1_).

If an intervention designed to improve chest wall compliance was administered before the age-related musculoskeletal changes in the thoracic spine and chest wall became irreversible, it could mitigate those changes and therefore have an impact on lung function [4–7].

Sandoz was the first to test this concept in 1976 when he proposed that altering the ’dynamic capabilities’ of the thoracic kyphosis would improve lung function [8]. In his seminal work, Sandoz administered a 6-week course of manual therapy (mobilisation or manipulation) to the thoracic spines of 20 women between the ages of 60 and 65. He found that both interventions produced clinically meaningful increases in lung function with manipulation producing a greater increase than mobilisation. Interestingly, he noted that the maximum improvement in lung function was reached after 3 weeks of either intervention, with no additional improvements achieved following a further 3 weeks of manual therapy. This means that there may be a functional limit to the effect that manual therapy can have on the reversibility of age-related declining lung function.

Others have repeated this experiment on younger people (18–28 years) with similar results [9–11]. However, those studies were conducted on small sample sizes and did not address Sandoz’s central issue of the reversibility of age-related lung function. This is the first fully powered trial designed to test this concept on healthy older people.

The aims of this trial are to investigate whether manual therapy can mitigate the effects of age-related changes in lung function and whether there is a difference in effect between two different forms of manual therapy.

## Methods/design

### Study design

The trial is designed as a randomised controlled trial and fulfils the requirements of the Standard Protocol Items: Recommendations for Interventional Trials (SPIRIT) checklist [12] (Additional file 1). The trial will evaluate 372 participants randomly allocated to three equal groups. Participants in Group 1 (Ex), the active control, will undertake a simple exercise program involving a standardised 10-min walking program performed on a treadmill. Participants in Group 2 (MB + Ex) will have manual therapy in the form of joint mobilisation (MB) administered to their thoracic spine and ribs prior to performing the same exercise regime as Group 1. Mobilisation consists of a pre-determined series of manoeuvres (mobilisation protocol) designed to increase joint mobility in the thoracic spine and rib cage (Grade III–IV mobilisation as per Maitland [13]). Participants in Group 3 (MT + Ex) will have manual therapy in the form of joint manipulation (manipulation protocol) administered to their thoracic spine and ribs prior to performing the same exercise regime as Group 1. Manipulation (MT) consists of two separate manipulations (Grade V mobilisation as per Maitland [13]), each involving a high velocity low amplitude (HVLA) thrust directed at the inter-vertebral, costo-vertebral and costo-transverse joints. The first manipulation will be delivered at the level of the upper/middle thoracic spine, while the second will be at the level of the middle/lower thoracic spine. Two different manipulation techniques are available under the trial’s manipulation protocol: supine and sitting. The supine technique, referred to as the ‘Opposite-side thenar/transverse drop’ [14] or ‘Supine wing’ [15] technique, can be delivered with the participant’s thoracic spine in flexion or extension. The sitting technique, referred to as a ‘Long-axis distraction’ [14] or ‘Sitting winglift’ [15] technique, can be delivered using an axilla or elbow hold. The choice of technique will be determined by the treating clinician based on biomechanical factors such as the patient-to-practitioner size ratio. All MT intervention will be administered as non-specific, multi-joint (group) manipulations. Administering MT in this way reduces the total number of manipulations required to address the thoracic spine within a single intervention session, as each manipulation has the potential to affect several thoracic vertebrae and their associated ribs simultaneously. All Ex will be performed immediately after MB and MT intervention, as this has been shown to enhance the synergistic effect of combining the two interventions [9, 16–18]. All intervention sessions will last between 15 and 20 min.

Participants will be recruited through self-referral in response to public advertisements placed in the local printed media and articles broadcast on the radio and/or television calling for volunteers for the trial. For logistical reasons the trial will be conducted at two sites: Southern Cross University’s Health Clinic in Lismore and Southern Cross University’s Health Clinic in the Gold Coast. The two sites will run sequentially with enrolment at the Gold Coast site not commencing until completion of the trial at the Lismore site. The main reasons for conducting the trial in this manner are recruitment and quality assurance. As Lismore is a medium-sized town in rural New South Wales (population 27,000), it is unlikely that the Lismore site will be able to generate sufficient participants for full enrolment. Adding the Gold Coast site, with its higher proportion of people over the age of 50, will improve the possibility of full enrolment. As the two sites are located approximately 98 km apart, achieving an acceptable level of quality assurance with the resources available mandates that the two sites be run consecutively.

### Outcome measurements

The primary outcome measure is lung function: FEV_1_ and FVC. The secondary outcome measures include chest wall expansion (tape measurements) and quality of life measurements (36-Item Short Form Health Survey, SF-36). The metric for these measures is mean change from baseline. All outcome measurements will be taken by blinded assessors on four occasions over a 9-week period: at baseline and then at weeks 3, 6 and 9.

### Participant characteristics

The trial includes both males and females between the ages of 50 and 65 years with no history of respiratory disease. Participants will be excluded if they have a history of respiratory disease, are currently smoking, cannot walk unaided and unassisted, have an existing diagnosis of osteoporosis or thoracic joint instability, present with acute pain on thoracic joint range of motion testing, have below normal chest wall musculature for their age and gender, exhibit a high level of anxiety related to receiving thoracic MB or MT or are contra-indicated for MB or MT as determined by a physical screening examination. Inclusion and exclusion criteria are described in Table 1.

**Table 1 Tab1:** Inclusion and exclusion criteria for participation

Inclusion criteria	Exclusion criteria
• Male and female • 50–65 years • No history of respiratory disease • Currently non-smoking (> 6 months) • Willingness to provide written consent • Willingness to participate in and comply with study requirements	• Inability to walk unaided and unassisted • Existing diagnosis of osteoporosis or thoracic joint instability • Present with: o Acute pain on thoracic joint range of motion testing o Below normal chest wall musculature o High level of anxiety related to receiving thoracic manual therapy o Contra-indicated for thoracic mobilisation and/or manipulation (physical screening examination) • Inability to understand English • Inability to provide informed consent, e.g. people with a cognitive impairment, intellectual disability or mental illness

